### Sample size

The sample size was calculated using the GPower software version 3.1.9.2 (Faul et al., 2007). The overall study objective is to test the hypothesis that association of anodic tDCS and sensory PES reduces pain intensity by a large percentage as opposed to use of isolated tDCS or PES in individuals with SCD. We assumed that the sample will be equally randomized into four intervention groups: (1) active tDCS + active PES; (2) active tDCS + Sham PES; (3) Sham tDCS + Active PES; and (4) Sham tDCS + Sham PES. We proceeded with the desired sample size assuming no financial or logistic limitations. The parameters used were: 80% power; 5% Type I error; effect size of 0.35 (Cohen, 1977) on the reduction of pain intensity evaluated by the VAS; four intervention groups; two genotypes (HbSS and HbSC) subgroups; and two repeated measures (pre- and post-intervention). Using these parameters yield to an estimated 64 participants for each genotype, a total *n* = 128. To increase the likelihood of achieve the computed sample size in a timely fashion, this clinical trial will be promoted through social media and posters in SCD treatment centers explaining the purpose and potential benefits of the study.

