## Methodology

### Study design, description of allocation, and blinding

This is a clinical, parallel, controlled, block-randomized, double blind trial. The study will occur in 2 days at the Clinical Electrophysiology Laboratory of the Federal University of Bahia, Brazil. An assistant researcher not involved in any other stage of the study will generate an allocation sheet (www.randomization.com) creating four groups for each SCD genotype (HbSS and HbSC), totaling eight experimental groups. Allocation concealment will be enforced using sealed opaque envelopes listed in ascending order, and the allocation secrecy will be maintained until the end of the analyses. The allocation envelope will be opened on the day of the intervention according to the order of inclusion of the study participant. The envelope will contain one of the following interventions: (1) active tDCS + active PES (*n* = 16); (2) active tDCS + sham PES (*n* = 16); (3) sham tDCS + active PES (*n* = 16); (4) sham tDCS + sham PES (*n* = 16) (Figure 1). These interventions will be tested either in the HbSS (*n* = 64), and HbSC (*n* = 64) groups, totalizing 128 participants.

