### Statistical analysis

To ensure impartiality of the results, researchers who do not participate in any stage of data collection will perform the statistical analysis. Descriptive statistic will be used to summarize demographic and clinical sample characteristics. Shapiro–Wilk test will be performed to test normality of the data. Chi-square test will be used to compare frequency distributions and one-way ANOVA or Kruskal–Wallis *H*-test will be used to compare baseline means among the four intervention groups. The main outcome of the study is pain rating measured by the VAS. For that, we will run a repeated measure analysis of variance (ANOVA) to evaluate differences among intervention groups (active tDCS + active PES; active tDCS + Sham PES; Sham tDCS + Active PES; and Sham tDCS + Sham PES), genotypes (HbSS and HbSC), and time (pre- and post-intervention). For most of the secondary outcomes (TMS volume map; TMS center of gravity; BDNF serum level; and TNF serum level) the repeated measures ANOVA will have the same three factors listed above. Relative EEG power will further include in the ANOVA the factors ROI (frontal, temporal, central, parietal, and occipital) and EEG condition (resting, Kinesthetic–MI of painful, and Kinesthetic–MI of non-painful region of the body). All analysis will be controlled for anxiety/depression symptoms. Bonferroni test will be used to correct for multiple comparisons. An α-value of 5% (*P* < 0.05) will be used to accept statistically significant differences for all analyses.

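### The stated 80% power at 128 participants matches an omnibus test across eight cells and is not shown to apply to the hypothesis that the combination beats each technique alone

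*Protocol article*

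**What the plan says.** The Sample size section ties the calculation to a directional comparison: "The overall study objective is to test the hypothesis that association of anodic tDCS and sensory PES reduces pain intensity" more than isolated tDCS or isolated PES. The Hypothesis section makes the same comparison for pain, and the Primary objective adds sham as a comparator.

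The inputs follow: "The parameters used were: 80% power; 5% Type I error; effect size of 0.35", with the effect size described as "on the reduction of pain intensity evaluated by the VAS; four intervention groups", two genotype "subgroups; and two repeated measures (pre- and post-intervention"). The result is "Using these parameters yield to an estimated 64 participants for each genotype, a total" of 128. The section on study design and allocation describes four interventions within each genotype, "totaling eight experimental groups", with 16 participants in each.

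The Statistical analysis section plans a repeated-measures ANOVA with intervention group, genotype and time as factors, and adds: "Bonferroni test will be used to correct for multiple comparisons". It does not say how many comparisons are meant. The article does not name the GPower procedure, does not give a pre-post correlation, and does not state a difference between the combination and a single technique.

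**The concern.** The hypothesis used to justify the sample size consists of two contrasts: combination against tDCS alone, and combination against PES alone. The listed inputs (one effect size, a number of groups, a number of measures) are those of an ANOVA F test, which asks whether any of the groups differ. The two questions have different power at the same sample size.

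Two misreadings are at stake. If the combination does not separate from a single technique, readers may take this as evidence from an 80%-powered comparison when the actual power could be far lower. Conversely, an omnibus test can be significant because the active arms differ from sham, even if the combination adds nothing to a single technique.

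**Working it through.** **Inputs.** From Sample size: power 80%, alpha 5%, effect size 0.35, four interventions, two genotypes, two measures, N = 128. From the design section: eight cells of 16, so 32 per intervention with genotypes pooled. Assumption: 0.35 is Cohen's f, the usual ANOVA metric in GPower.

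**Step 1: reproduce 128.** For an omnibus F test over eight cells, λ = N·f², with 7 and N − 8 degrees of freedom.
- N = 128 (16 per cell): λ = 128 × 0.35² = 15.68, df 7 and 120, power 81.4%.
- N = 120 (15 per cell): λ = 14.70, df 7 and 112, power 78.2%.
- The smallest N reaching 80% is 125, which becomes 128 with equal cells.

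The stated figure is reproduced. The same λ and degrees of freedom arise in two ways: a one-way ANOVA over the eight cells, or a group-by-time test in which f is defined on the pre-post change.

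**Step 2: other routes.** GPower-type repeated-measures formulas with eight groups, two measures and correlation 0.5 need 37 in total for the within-between interaction (40 balanced) and 96 for the between-groups effect. Neither is 128. The between-groups formula gives 64 with four groups and a correlation of about 0.30 (64 per genotype), and 128 with eight groups and a correlation of about 0.95. Neither correlation is stated. Both are omnibus tests as well.

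**Step 3: translate f = 0.35 into contrasts.** Assume that f = 0.35 describes the spread of the four arm means of pain reduction in SD units. Here f is the root mean square deviation of the arm means from their average.
- Additive pattern (sham 0, each single a, combination 2a): f = √[(a² + 0 + 0 + a²)/4] = a/√2, so a = 0.35 × √2 = 0.495. Combination minus single is d = 0.495.
- Combination-only pattern (0, 0, 0, d): f = d·√(3/16), so d = 0.35/0.433 = 0.81.

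**Step 4: power per contrast.** Noncentral t with 120 df and noncentrality d·√(32/2) = 4d, which is 1.98 for the additive pattern and 3.23 for the combination-only pattern. Power to beat both singles is by simulation with pooled error; that joint criterion is an assumption.

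| Pattern | Quantity | 5% unadjusted | Bonferroni, 2 | Bonferroni, 6 |
|---|---|---|---|---|
| Additive, d = 0.495 | one contrast | 50% | 39% | 25% |
| Additive | both singles beaten | 34% | 23% | 12% |
| Combination-only, d = 0.81 | one contrast | 89% | 83% | 71% |
| Combination-only | both singles beaten | 82% | 73% | 57% |

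**Step 5: difference detectable with 80% power.** Solving the noncentral t for one contrast of 32 vs 32 gives 0.71 SD at two-sided 5%, 0.78 SD with Bonferroni over two and 0.88 SD over six.

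**Step 6: the intervention main effect.** The 3-df test across the four arms with f = 0.35 and N = 128 has λ = 15.68, df 3 and 120, and power 92%. This holds for any arm pattern with f = 0.35, including one in which all three active arms are equal and differ only from sham.

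**The case against.** The strongest defence is that nothing has been miscalculated. The planned primary analysis is a repeated-measures ANOVA followed by Bonferroni, so sizing for an omnibus test agrees with the stated analysis, and 128 is correct for such a test. Details of the contrasts may also sit in an analysis plan that is not shown. All of this stands. It does not remove the mismatch, because the article itself offers the 80% as support for the combination-against-single hypothesis.

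A second objection is that the low figures depend on assumed patterns. This stands too. The article gives no arm means, no SD and no number of comparisons. The Hypothesis section suggests two comparisons, sham would make three, and six is the number of all pairs of arms. In the combination-only pattern, each contrast exceeds 80% unadjusted and with Bonferroni over two. The additive pattern nevertheless deserves weight: the Introduction describes the two analgesic effects as summing, and the section on potential pitfalls frames the main question as one of additivity.

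Three stronger readings are tempting but not supported:
- *The two repeated measures were ignored.* A group-by-time test on the pre-post change gives the same 128, and the effect size is described as being on pain reduction. On that reading, a genotype difference in pain level alone would not drive the test.
- *128 is adequate for the eight-cell test and nothing else.* The 3-df arm effect has 92% power at the same f.
- *Each genotype's 64 is underpowered on its own.* A four-arm one-way test on 64 has 61% power, but a repeated-measures route with a correlation of about 0.30 gives exactly 64, and the document does not settle which was meant.

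**Conclusion.** The point holds as a mismatch between the powered test and the stated hypothesis; it is not an arithmetic error. Every route found to 64 or 128 is an omnibus test, so the conclusion does not depend on which one the authors used. That 128 came from the eight-cell test is an inference from the exact match.

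The actual power for combination against a single technique cannot be fixed from the article. Under the stated assumptions it runs from 25% to 89% per contrast. In the additive pattern, which is the trial's own premise, it is at most 50%. If both singles must be beaten, the range is 12% to 82%, and 80% is reached only in the combination-only pattern without multiplicity correction. It would be wrong to infer that the trial is underpowered for every question, or that the contrasts must have low power; the 80% is simply not shown to belong to them.

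**What to change.** Keep 128 and revise the Sample size paragraph to:
1. name the GPower test, say what f = 0.35 measures (between-cell spread, or spread of the pre-post change), and give the correlation if one was used;
2. state that the 80% refers to that omnibus test;
3. state that each combination-against-single contrast (32 vs 32, genotypes pooled) has 80% power to detect about 0.71 SD of pain reduction at two-sided 5%, 0.78 SD with Bonferroni over two comparisons, or 0.88 SD over six;
4. state which number of comparisons applies and, if both singles must be beaten, say so and give the power for that.

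The cost is rewording. No participants, arms or procedures change. The downside is that the published power statement becomes less favourable.

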### Statistical analysis

To ensure impartiality of the results, researchers who do not participate in any stage of data collection will perform the statistical analysis. Descriptive statistic will be used to summarize demographic and clinical sample characteristics. Shapiro–Wilk test will be performed to test normality of the data. Chi-square test will be used to compare frequency distributions and one-way ANOVA or Kruskal–Wallis *H*-test will be used to compare baseline means among the four intervention groups. The main outcome of the study is pain rating measured by the VAS. For that, we will run a repeated measure analysis of variance (ANOVA) to evaluate differences among intervention groups (active tDCS + active PES; active tDCS + Sham PES; Sham tDCS + Active PES; and Sham tDCS + Sham PES), genotypes (HbSS and HbSC), and time (pre- and post-intervention). For most of the secondary outcomes (TMS volume map; TMS center of gravity; BDNF serum level; and TNF serum level) the repeated measures ANOVA will have the same three factors listed above. Relative EEG power will further include in the ANOVA the factors ROI (frontal, temporal, central, parietal, and occipital) and EEG condition (resting, Kinesthetic–MI of painful, and Kinesthetic–MI of non-painful region of the body). All analysis will be controlled for anxiety/depression symptoms. Bonferroni test will be used to correct for multiple comparisons. An α-value of 5% (*P* < 0.05) will be used to accept statistically significant differences for all analyses.

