### Outcome measures

#### Primary outcome measure

Pain intensity will be measured by the VAS, in two positions: participant sited comfortably and then sited abducting the most painful hip. The VAS ranges from zero to 10, where zero represents no pain at all and 10 the worst imaginable pain. This evaluation will be performed pre- and post-intervention.

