*Stage 1* (Sample characterization) will last ~40 min. The researcher will explain to the participant why and how to fill the socio-demographic and clinical questionnaires. The researcher will be available to clarify any doubts and help participant, if requested;*Stage 2* (Baseline assessment). EEG data will be collected during resting and Kinesthetic–MI conditions. Subsequently, in another room, the participant will receive instructions for the TMS cortical mapping. Following these electrophysiological assessments, a blood sample will be collected for BDNF and TNF serum level analysis. Finally, the pain intensity will be assessed. This stage may last up to 1 h and 30 min;*Stage 3* (Intervention). At this stage, the participant will be seated and the researcher will position the tDCS electrodes on the scalp according to the 10/20 EEG system. Electrodes will be fixed with an elastic band, comfortably adjusted. The PES electrodes will be positioned at the most painful hip. This stage will last around 40 min;*Stage 4* (Post-intervention assessment). In the last part of the study, the sequence of assessments will be slightly different from Stage 2. First, pain intensity will be measured. Then, a blood sample will be collected. Blood sample must be collected earlier in this stage to reduce circadian cycle effect on BDNF and TNF serum levels (Pan et al., 1985; Begliuomini et al., 2008). Finally, EEG data and TMS cortical mapping will be collected. The final stage is expected to last up to 1 h and 30 min.

Participants may take 5–10 min-breaks between all stages. During their time in the laboratory room, participants will have snacks and light beverage available at breaks. Participants will be reimbursed for transportation costs and receive a food voucher at the end of data collection.

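### Baseline VAS enters the primary analysis only as a level of the time factor; using it as a covariate would give a more precise treatment comparison from data already collected

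*Protocol article*

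**What the plan says.** The Statistical analysis section fixes the model for pain intensity: "we will run a repeated measure analysis of variance (ANOVA) to evaluate differences among intervention groups", with the further factors "genotypes (HbSS and HbSC), and time (pre- and post-intervention". The covariate adjustment is one sentence: "All analysis will be controlled for anxiety/depression symptoms". Genotype is therefore in the model as a factor, and the anxiety/depression score is the only covariate. The Potential confounders section names no other covariate for pain.

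Baseline pain is available for everyone. The Primary outcome measure section says of the VAS: "This evaluation will be performed pre- and post-intervention". Under Stepwise procedures, it is the last item of the baseline stage ("Finally, the pain intensity will be assessed") and the first item of the post-intervention stage. No section enters it as a covariate. Baseline means are only compared among the four groups.

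The Sample size section gives its parameters as "80% power; 5% Type I error; effect size of 0.35 (Cohen, 1977) on the reduction of pain intensity evaluated by the VAS". It crosses the interventions with genotype, counts one measurement on each side of the session, and arrives at 64 per genotype, 128 in total. The same three-factor model is planned for TMS map volume, TMS centre of gravity, BDNF and TNF.

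**The concern.** In a randomised trial with one pre and one post measurement, the baseline value of the outcome can be used in two main ways. It can be subtracted, which sets its coefficient to 1, or it can be a covariate whose coefficient is estimated. A repeated-measures ANOVA with a two-level time factor does the first. Both give an unbiased treatment comparison, but subtraction carries the noise of the baseline measurement into the outcome whenever the true slope is below 1.

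What is at stake is precision, not validity. The trial has 32 participants per intervention (16 in each genotype), and its objective is to separate the combined treatment from each single technique and from sham. Precision given up here cannot be recovered by adjusting for anxiety and depression, and it is precision the trial has already paid for by measuring VAS before the session.

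**Working it through.** **Inputs from the protocol article.** Four interventions by two genotypes, 8 cells of 16, N = 128; effect size f = 0.35 on the reduction in VAS; alpha 5%; target power 80%; two measurements. **Assumption.** The pre-post correlation rho is not given, so 0.3 to 0.9 is shown.

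**1. Reproducing N = 128.** The article does not say which G*Power routine was used. An omnibus F test across the 8 cells, applied to the change score, reproduces the figure:
- noncentrality = f² × N = 0.1225 × 128 = 15.68
- degrees of freedom 7 and 128 − 8 = 120
- power = 81.4%

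Power first reaches 80% at N = 125, which rounds up to 128 with 8 equal cells. A 3-df test of the four interventions would need only 96. The 8-cell change-score test is therefore used as the reference.

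**2. Group-by-time is a change-score test.** With two time points, the within-subject part of the model depends on the data only through post minus pre. With common standard deviation s at both times:
- Var(change) = 2(1 − rho)s²
- Var(post given baseline, ANCOVA) = (1 − rho²)s²
- ratio = (1 − rho²) / [2(1 − rho)] = (1 + rho)/2

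The ratio is below 1 for every rho below 1. If the pre and post variances differ, the fitted slope still minimises the residual variance, so ANCOVA cannot do worse apart from the degree of freedom it uses.

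**3. Effect on the reference test.** The noncentrality becomes 15.68 / [ratio × (1 + 1/117)], with 7 and 119 degrees of freedom. The factor 1 + 1/117 charges for estimating the slope. For example, at rho = 0.5: 15.68 / (0.75 × 1.00855) = 20.73.

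| Assumed rho | Variance ratio | Reduction in standard error | Power at N = 128 (81.4% as planned) | N for 80% power, equal cells |
|---|---|---|---|---|
| 0.3 | 0.65 | 19% | 95.7% | 88 |
| 0.5 | 0.75 | 13% | 92.1% | 104 |
| 0.7 | 0.85 | 7% | 87.9% | 112 |
| 0.8 | 0.90 | 5% | 85.6% | 120 |
| 0.9 | 0.95 | 2% | 83.3% | 120 |

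**4. Does the anxiety/depression adjustment recover the loss?** A simulation with 8 cells of 16 and such a covariate in both models gave variance ratios of 0.73 to 0.75 at rho 0.5, 0.84 to 0.85 at 0.7 and 0.88 at 0.8. These are close to (1 + rho)/2, so it does not.

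**The case against.** The strongest defence is that nothing here is an error. The group-by-time test is valid, baseline is used through subtraction, and the sample size was set for a reduction in pain. Read that way, the planned test meets its own 80% target. All of this stands: ANCOVA adds margin and does not rescue a failing design. A reader might infer that the trial is underpowered as planned, but the documents do not support that.

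A second defence is that rho may be high, because VAS is taken last before and first after a session of about 40 minutes on the same day. That also stands, and it is why the table runs to 0.9, where the gain is about two percentage points of power.

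Two stronger readings are tempting:
- **Diluted main effect.** A reader might infer that the planned test is the group main effect, which averages pre and post scores and so halves the treatment effect. The primary objective speaks of reducing pain, the sample size is based on the reduction, and time is a named factor. These point to group-by-time. The main effect is at most a possible reading.
- **Inflated familywise error.** A reader might count four model terms containing intervention, each at 5%, and compute 1 − 0.95⁴ = 18.5%. The same section plans a Bonferroni correction for multiple comparisons, although its scope is not spelled out. Response by genotype is a secondary objective, so its terms are not rival primary results. The figure is not supported.

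**Conclusion.** The point holds as one of efficiency. The planned analysis is valid, but it is less precise than a baseline-adjusted ANCOVA for any rho below 1. At rho 0.3 to 0.7 the variance falls by 35% to 15%, and power on the reproduced test rises from 81.4% to between 95.7% and 87.9%. At 0.8 the gain is modest, and at 0.9 it is small.

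These sizes rest on three things: an assumed rho, equal pre and post variances, and reading f = 0.35 as an 8-cell change-score effect, which is the reading that returns 128. The direction of the result depends on none of them, apart from the one degree of freedom. The change is worth making because it needs nothing the trial does not already collect.

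**What to change.** In the Statistical analysis section, make the primary analysis an ANCOVA of post-intervention VAS on intervention group, with these terms:
- baseline VAS measured in the same position as the outcome, since VAS is taken both at rest and during hip abduction
- genotype, within which the allocation is generated
- the anxiety/depression score, as already planned

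Read the treatment result from the group contrasts of the combined treatment against each single technique and against sham, using the Bonferroni correction already planned. Test group-by-genotype as the secondary question. Use the same model for TMS volume, centre of gravity, BDNF and TNF, each with its own baseline.

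The cost is a change of wording and one error degree of freedom out of about 119. No extra measurement, visit or participant is needed, and the sample size can stay at 128.

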#### Secondary outcome measures

A. Power density of electroencephalographic frequencies

Relative power density will be measured pre- and post-intervention. An electroencephalograph (EEG Brainet 36, EMSA, Brazil) with 30 electrodes arranged according to the international system of electroencephalography 10/10 will be used in the following electrode locations: F7 T3 T5 Fp1 F3 C3 P3 O1 F8 T4 T6 Fp2 F4 C4 P4 O2 Fz Cz Pz Oz FT7 FT8 TP7 CP3 FC3 CPz FCz CP4 FC4 TP8. EEG data will be collected at a sampling rate of 600 Hz and referenced to Cz channel. Impedance will be maintained below 5 kΩ for all electrodes. The recording environment will be kept in subdued light and protected by a Faraday cage. Participants will be instructed to sit comfortably in a chair, keeping their eyes closed during EEG recording, which will occur in the two conditions described below.

a. Resting state: This condition will last 4 min, and the participant will be asked to not focus on any specific cognitive activity;b. Kinesthetic motor imagery (Kinesthetic–MI): Kinesthetic–MI will follow the resting state recorded, divided into two distinct stages. (1) *Kinesthetic–MI of a movement in the non-painful region of the body:* After 10 s of recording, participants will hear a standardized command requesting to mentally simulate closing and opening the contralateral hand to the most painful hip side. The command to each mental simulation will be repeated eight times, being 5 s of closing movements and 10 s of opening movements of the hand, totaling 120 s. (2) *Kinesthetic–MI of a movement in the painful region of the body:* The same protocol described above will be repeated, but this time the command will be to mentally simulate the abduction and adduction of the most painful hip. Electromyographic (EMG) data of the *gluteus medius* muscle on the most painful side and flexor muscles of the fingers contralateral to the hip will be also recorded to ensure absence of real movement. After each recording, the quality of the Kinesthetic–MI will be assessed by the kinesthetic and visual imagery questionnaire (KVIQ) (Malouin et al., 2007). EEG recording will take ~1 h.

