Pre-processing of EEG data will be done using the MATLAB software version 2015 and EEGlab *toolbox* version 14. The signals will be filtered offline with a bandpass between 0.5 and 45 Hz. EEG data will be segmented into epochs of 1.71 s to allow an analysis of power densities at frequencies ranging from 1.2 to 30 Hz. EEG artifacts with minimum amplitude below −750 or maximum amplitude above 750 μV will be rejected using a semi-automated protocol. EEG data with more than 33% of rejected epochs will be excluded from further analyses. After the artifact rejection protocol, all EEG data will be adjusted to have the same number of epochs.

Power density will be calculated by fast Fourier transform in each epoch and electrodes, separately for each participant. The average power densities will be grouped in delta (1.2–3.5 Hz), theta (4–7 Hz), alpha (8–12 Hz), and beta (13–30 Hz) frequency bands. Regions of interest (ROI) chosen for analysis will be computed by averaging power densities for the following groups of electrodes: frontal (F7, F3, Fp1, Fz, Fp2, F4, F8), central (FC3, C3, FCz, Cz, C4, FC4), parietal (CP3, P3, CPz, Pz, CP4, P4) temporal (FT7, T3, TP7, T5, FT8, T4, TP8, T6), and occipital (O1, Oz, O2). After obtaining absolute power densities, the relative power density will be calculated dividing electrode's values in each one of the analyzed frequencies by their values in the total power spectrum.

B. TMS cortical mapping

Cortical mapping will be assessed pre- and post-intervention. After EEG recording, each participant will be asked to lie down comfortably in a supine position on an examination table, with head and neck resting on a support. The TMS cortical mapping will be performed using a single-pulse TMS apparatus (Bi-Stim; Magstim Co. Ltd, Dyfed, UK) delivered over M1 to cover the representation of both *gluteus maximus* muscles. A figure-of-eight coil will be positioned with the handle oriented backwards and aligned to the sagittal suture, inducing a postero-anterior flow of current. One cap marked with an 8 × 7 cm grid and oriented to the vertex will be placed on the participant's head and regularly checked to guarantee placement consistency. The vertex will be marked on the intersection of interaural and nasion to inion lines according to the 10/20 international EEG system.

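### The repeated-measures ANOVA planned for EEG power can lose a whole participant to one unusable recording; a mixed model would keep the rest (optional, one secondary outcome)

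*Protocol article*

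**What the plan says.** The protocol article, under Secondary outcome measures (part A), sets two time points: "Relative power density will be measured pre- and post-intervention". Each includes three conditions: 4 min of rest, a 120 s block of hand imagery and a 120 s block of hip imagery.

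The same part describes the cleaning. "EEG data will be segmented into epochs of 1.71 s", and epochs whose amplitude goes beyond ±750 μV "will be rejected using a semi-automated protocol". Then: "EEG data with more than 33% of rejected epochs will be excluded from further analyses". The next sentence reads: "After the artifact rejection protocol, all EEG data will be adjusted to have the same number of epochs". The article does not say whether the 33% is counted per recording, per session or per participant.

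Under Statistical analysis, the main model is a repeated-measures ANOVA with intervention group, genotype and time. For EEG it is extended: "Relative EEG power will further include in the ANOVA the factors ROI (frontal, temporal, central, parietal, and occipital) and EEG condition". All analyses are adjusted for anxiety and depression symptoms. The article names no mixed model for EEG.

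**The concern.** A classical repeated-measures ANOVA, as standard software runs it, uses only participants with every within-subject cell filled. Here the within-subject factors are time (2), condition (3) and ROI (5). An excluded or missing recording empties five cells at once, and the participant's other five recordings go with it.

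Gaps can be foreseen from the article itself. The 33% rule creates them if it applies per recording. The Discontinuity criteria stop participants with a moderate or severe adverse effect during evaluation or intervention, which can leave baseline EEG only.

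What is at stake is precision for the EEG hypothesis (lower delta, theta and alpha power under the combined intervention). The complete cases could also be a selected subset if failures relate to the participant's state, but nothing in the article shows that this will happen.

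**Working it through.** **Inputs from the article.** Times: 2. Conditions: 3. ROIs: 5. Participants: 128, which is 8 cells (4 interventions × 2 genotypes) of 16. Epoch length: 1.71 s. The 128 was sized on VAS pain and not on EEG; the article has no EEG figure to reproduce.

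**Recordings.** 2 × 3 = 6 per participant, and 6 × 128 = 768 in total.

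**What the unit of the 33% rule changes.**
- Epochs at rest: 240 / 1.71 ≈ 140. Epochs per imagery block: 120 / 1.71 ≈ 70.
- Per recording: an imagery block is excluded once about 0.33 × 70 ≈ 23 epochs fail, which is about 40 s of signal.
- Per session: 140 + 70 + 70 = 280 epochs. A wholly lost imagery block is 70 / 280 = 25%, so nothing is excluded.
- Per participant: 560 epochs. The same block is 70 / 560 = 12.5%, so again nothing is excluded.

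Only the per-recording unit lets one bad imagery block trigger the rule.

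**Loss under the per-recording unit.** Let q be the probability that a recording is unusable. The article does not give q, so the values below are assumptions. With independent failures, the share of participants lost is 1 − (1 − q)^6. Usable recordings number 768(1 − q), and complete-case analysis uses only 768(1 − q)^6 of them.

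| q (assumed) | (1 − q)^6 | Participants lost | Complete, of 128 | Usable recordings | Usable but discarded |
|---|---|---|---|---|---|
| 1% | 0.9415 | 5.9% | 120.5 | 760 | 37 |
| 2% | 0.8858 | 11.4% | 113.4 | 753 | 72 |
| 5% | 0.7351 | 26.5% | 94.1 | 730 | 165 |
| 10% | 0.5314 | 46.9% | 68.0 | 691 | 283 |

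**Clustered failures.** In a beta-binomial model with an assumed within-participant correlation of 0.2 to 0.5, the loss at q = 5% is 18% to 12%, and at q = 10% it is 34% to 22%.

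**Precision.** Complete-case variance grows by roughly 1 / (1 − q)^6: a rise of 13% at q = 2%, 36% at 5% and 88% at 10%. Simulation of the arm contrast on pre-post change, with six recordings per participant, no ROI factor and assumed variance components, gives:

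| Failures | q | Variance rise, complete cases | Variance rise, all usable recordings |
|---|---|---|---|
| Independent | 2% | 13–14% | 1–2% |
| Independent | 5% | 37–39% | 3–6% |
| Independent | 10% | 91–97% | 7–13% |
| Clustered (0.3) | 2% | 7% | about 2% |
| Clustered (0.3) | 5% | 19–20% | 4–6% |
| Clustered (0.3) | 10% | 43–45% | 9–13% |

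Because ROI is left out, these figures show the direction and rough size of the gain, not the exact gain for the five-factor EEG model.

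**The case against.** **The unit is not stated.** A reader might infer that the plan excludes recordings one by one. It does not say so. The sentence on equalising epochs treats the data as separate sets, and imagery quality is rated after each recording, so per recording is the natural reading. It remains a reading. Under a pooled rule only unfinished or abandoned recordings would leave gaps.

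**Listwise deletion is not a stated rule.** It follows from how the named method is usually run. The handling of missing cells may sit in an analysis plan that is not shown, and its absence from an article is no finding. That stands. What remains is narrower: the article names a model that copes poorly with the gaps its own cleaning rule can create.

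**The rate may be low.** The amplitude limits are wide, and more than a third of epochs must fail before data are excluded. Recording is seated with eyes closed, in a Faraday cage, at impedances below 5 kΩ. A reader might take losses of 26% or 47% as expected; the article does not support that. Nor are the complete cases a group free of artifacts, since recordings with up to 33% rejected epochs are kept.

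**A mixed model is not automatically better.** A random intercept alone imposes compound symmetry, which is stricter than sphericity. A fully unstructured covariance over 2 × 3 × 5 = 30 cells has 30 × 31 / 2 = 465 parameters for 128 participants. Both points are correct and shape the fix.

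**Conclusion.** The point holds as a modest one. The article fixes a repeated-measures ANOVA over time, condition and ROI, alongside an exclusion rule whose unit is open. On the per-recording reading, or when a post-intervention recording is missing, the usual ANOVA throws away usable data. The loss is about 6% of participants at an assumed 1% failure rate and 11% at 2%. It reaches 26% and 47% only at 5% and 10% with independent failures, and is smaller under clustering.

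A reader might infer that the EEG result will be biased or that the trial's main conclusion is weakened. The article supports neither. No differential loss is shown, and the VAS primary outcome and its sample size are untouched. The consequence is a possible loss of precision, of unknown size, on one secondary outcome. Priority: optional, low.

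**What to change.** 1. State that the 33% rule applies to each recording (one condition at one time).
2. Analyse relative EEG power with a linear mixed model that has the same fixed factors (intervention group, genotype, time, condition, ROI) and the anxiety/depression covariate, fitted to every recording that passes.
3. Prespecify the covariance in one of two ways:
   - random effects for participant and for participant-by-time, participant-by-condition and participant-by-ROI; or
   - a separate model for each ROI with an unstructured 6 × 6 covariance over time and condition, which has 6 × 7 / 2 = 21 parameters.

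   Neither a random intercept alone nor an unstructured 30 × 30 covariance is suitable. The 6 × 6 option drops the sphericity assumption for time and condition, but gives up the comparison of ROIs within one model.

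**Cost.** A few sentences in the analysis section and no new data. With complete, balanced data and a matching random-effects structure, the result is essentially that of the ANOVA. The downside is that the covariance structure must be chosen in advance and the model relies on data missing at random. It would therefore not correct for exclusions that depend on the unseen EEG values.
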